Children are followed up at weeks 6 and 12 after starting treatment. During the first 3 days after enrollment, they are visited at school or home daily to administer study treatment and complete the adverse events questionnaire. At the week 6 and 12 follow-up visit, the children provide an early morning stool sample, and the study clinician takes a brief medical history, performs a clinical examination, and obtains a fingerprick blood sample for hemoglobin estimation. Participants who do not return for the scheduled follow-up visits are visited at home.

A detailed schedule of the study procedures at different time points is presented in Table 1.

**Table 1 Tab1:** Scheduled visits and procedures

	Enrollment/baseline	Allocation	Intervention (3 days)			Follow-up	
	− D5	D0	D0	D1	D2	Week 6	Week 12

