### Hemoglobin assessment

The study clinician takes a fingerprick blood sample at screening and week 6 and week 12 follow-up visits to determine the hemoglobin level. The hemoglobin level is estimated using a portable hemoglobinometer (HemoCue Hb 301, HemoCue, Angelholm, Sweden). The hemoglobin value obtained is categorized according to the WHO criteria [31].

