### Data management and analysis

Data collected from each participant is recorded on paper-based case report forms (CRFs) in black ballpoint pen. The principal investigator will ensure that the data in the CRFs are accurate, complete, and legible. Data from the case record forms is entered by a data clerk into computers as they accrue using the MS Access program. The data is verified by comparing it with the CRFs. Missing data is imputed as either treatment success or treatment failure (assuming the same infection intensities before and after treatment). Validated data is transferred to SPSS version 20 and STATA version 12 for statistical analyses. The CRFs and the electronic data will be kept for 5 years after the primary manuscripts are published.

Data is analyzed using SPSS for Windows version 20 (SPSS Inc., Chicago, IL) and STATA version 12.0 (StataCorp., College Station, TX, USA) packages. A two-sided *p*-value less than 0.05 is considered statistically significant for all tests.

Demographic and other baseline characteristics are compared to check for imbalances between the study groups. These measures will be tabulated from the intent-to-treat population. Significance tests are not performed to compare the differences between study groups at baseline. Where imbalances are suspected, additional analyses are performed to adjust for these variables.

To determine efficacy, both the per-protocol and intention-to-treat analyses are done, but the per-protocol analysis is the main approach. The primary efficacy outcome is the cure rate, defined as the proportion of children infected with *S. mansoni* at enrollment but not excreting eggs by week 6 after taking the study treatment. In the computation of the cure rate, children randomized to the PZQ alone study arm are considered the control group. Cure rates are compared between the treatment groups using Pearson’s chi-square test for contingency tables (in a per-protocol analysis) and summarized as absolute risk differences with 95% confidence intervals (CI). The per-protocol population is defined to include all participants who were randomized and who completed the study procedures to week 6 or 12. The primary hypothesis for non-inferiority is assessed by considering the lower limit of the 95% CI for the risk difference. Non-inferiority is concluded if the lower bound of the 95%CI from the risk difference does not exceed the non-inferiority margin of − 10.

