The cumulative cure rate at week 12 is assessed by calculating a two-sided difference in proportions of cured children from each PZQ plus ACT arm compared with the PZQ alone arm. Arithmetic mean (AM) egg counts are computed for all non-cured participants. The egg reduction rate is computed as (1 − (AM EPG after treatment/AM EPG before treatment)) × 100. The ERR is expressed as a percentage. Re-infection rate is the proportion of children who test negative for *S. mansoni* at week 6 but test positive at week 12 follow-up. Changes in continuous variables over time are assessed using analysis of variance (ANOVA). The least significant difference will be used to assess post hoc pair-wise comparisons between the group means. Logistic regression will be used for analyses adjusted for the treatment received.

For the primary safety analysis, the frequency and pattern of adverse events are computed by patient counts and percentages in each of the five treatment groups. Adverse events are computed for all participants who received at least one dose of the study drug (intention-to-treat population).

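### ANOVA of changes over time, with baseline adjustment only where imbalance is suspected, is valid on its natural readings but less precise than pre-specified adjustment for each child's baseline

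*Protocol article*

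**What the plan says.** All references are to the protocol article.

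- **Method.** Data management and analysis states "Changes in continuous variables over time are assessed using analysis of variance (ANOVA". It then adds: "The least significant difference will be used to assess post hoc pair-wise comparisons between the group means". No child effect, repeated-measures term or baseline covariate is attached to this method.
- **Baseline adjustment.** The same section foresees it only conditionally: "Where imbalances are suspected, additional analyses are performed to adjust for these variables". It gives no rule for when an imbalance counts as suspected.
- **Repeated measurements.** Under Hemoglobin assessment: "The study clinician takes a fingerprick blood sample at screening and week 6 and week 12 follow-up visits to determine the hemoglobin level". Table 1 schedules weight and height at the same three points. Stool is examined at screening and at both follow-up visits.
- **Egg counts.** Arithmetic mean counts are computed for the non-cured participants. The next sentence gives the summary measure: "The egg reduction rate is computed as (1 − (AM EPG after treatment/AM EPG before treatment)) × 100".
- **Primary outcome.** This is a proportion, handled separately: "Cure rates are compared between the treatment groups using Pearson’s chi-square test for contingency tables (in a per-protocol analysis").

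**The concern.** The trial collects a pre-treatment value of each continuous variable on every child, but the main analysis does not commit to using it as a covariate. Subtracting the baseline, as a change score does, removes the right amount of baseline variation only when the within-child correlation is 1. At any lower correlation it over-corrects. The between-arm difference then carries extra noise, and part of any chance baseline imbalance passes into it with reversed sign.

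The conditional route to adjustment does not remove this. It is an additional analysis, its trigger is not defined, and the Randomization and blinding section says that the data analysts are not blinded. Fixing the adjustment in advance avoids a choice made after looking at the data.

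For egg counts there is a second problem. A mean taken only over children who were not cured compares groups formed by the treatment's own effect, so the arms no longer have the balance that randomization gave them.

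What is at stake is precision for hemoglobin and weight, and interpretability of any egg-count comparison. The non-inferiority conclusion on cure is not at stake.

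**Working it through.** **Inputs.** The protocol states no standard deviation, no within-child correlation and no target precision for these variables, so there is no figure of its own to reproduce. The within-child correlation r is therefore an assumption, shown from 0.3 to 0.7 with 0.9 added. The protocol supplies 102 children per arm and a 72% cure rate on praziquantel (62% at the margin), all from Sample size.

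**Step 1: variance of a between-arm comparison at one follow-up visit.** Take equal variance at baseline and follow-up, the same r in each arm, and express variance relative to a comparison of follow-up values alone (= 1).

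- Change score: 2(1 − r)
- Adjusted for baseline (ANCOVA): 1 − r²
- Ratio: 2(1 − r) / [(1 − r)(1 + r)] = 2/(1 + r)

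| Assumed r | Change score | ANCOVA | Variance ratio | SE ratio | 102 per arm is worth, 102 × (1 + r)/2 |
|---|---|---|---|---|---|
| 0.3 | 1.40 | 0.91 | 1.54 | 1.24 | 66 |
| 0.5 | 1.00 | 0.75 | 1.33 | 1.15 | 76 |
| 0.7 | 0.60 | 0.51 | 1.18 | 1.08 | 87 |
| 0.9 | 0.20 | 0.19 | 1.05 | 1.03 | 97 |

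At r = 0.5 the loss equals discarding a quarter of the children (1 − 1/1.33 = 0.25). For a variable that tracks closely within a child, as body weight may, the loss is small.

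**Step 2: repeated-measures ANOVA.** With one baseline and one follow-up, its arm-by-time test is the change-score test, so the ratios in Step 1 apply to it as well. It is valid: in a simulation with 102 children, three visits and r of 0.3, 0.6 and 0.8, its test of a time effect rejected in 5.0% to 5.3% of 2,000 null runs at a nominal 5%.

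**Step 3: does the direction depend on equal variances?** With standard deviations s0 at baseline and s1 at follow-up, the change-score variance is s1² + s0² − 2r·s0·s1, and the ANCOVA variance is s1²(1 − r²). The difference is (s0 − r·s1)², which is never negative. So baseline adjustment is never less precise in large samples. The sizes in Step 1 do need equal variances. They should not be carried over to raw egg counts, whose spread should change sharply after treatment.

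**Step 4: egg counts among the non-cured.** At 72% cure, 0.72 × 102 ≈ 73 children per arm have a zero count at week 6 and about 29 remain. The mean over all children equals the non-cured share times the mean among the non-cured. Suppose one arm cures 72%, another cures 62%, and the mean count m among the non-cured is the same in both. The non-cured means then show no difference, while the means over all children are 0.28m and 0.38m. The second is 36% higher (0.38/0.28 = 1.36). The restriction hides exactly the part of the effect that comes from cure.

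**The case against.** The strongest reply is that the protocol does not say what a critic might take from it. A reader might infer that visits are analysed as if they came from different children. On that reading the standard error of a change over time would be too large by 1/√(1 − r), or 1.20 to 1.83 for r of 0.3 to 0.7. Pooling weeks 6 and 12 as independent rows would raise the simulated false-positive rate for the five-arm comparison to 11%, 21% and 26% at r of 0.3, 0.6 and 0.8. But the text states neither practice. An analysis of changes over time is naturally read as change from the child's own baseline or as repeated-measures ANOVA. Both respect the pairing, and a change score uses the baseline by construction. This part of the reply stands in full.

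It is also true that hemoglobin and weight are not listed under Outcomes, that cure and re-infection are proportions, and that the egg reduction rate has its own formula. So it would be too strong to say that the listed secondary outcomes are weakened in general. Replacing the arithmetic-mean measure by one on log(EPG + 1) would change the quantity estimated rather than correct an error. Both points stand.

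The last argument is that the model form belongs in an analysis plan that is not shown. This carries less weight. The protocol names the method and places baseline adjustment in a conditional, additional role, so this is a stated choice that can be improved and not merely a missing detail.

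**Conclusion.** The point holds as an improvement to a valid analysis. It does not show that the planned standard errors are wrong; they would be wrong only if visits were treated as independent, which the text does not say. On the change-score or repeated-measures reading, the between-arm comparison has 2/(1 + r) times the variance of a baseline-adjusted one: 54% more at r = 0.3, 33% at 0.5, 18% at 0.7. These sizes rest on assumed correlations and on equal variances before and after treatment. The direction does not depend on equal variances.

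The scope is hemoglobin, weight and any egg-count comparison. The primary cure-rate analysis is untouched. The restriction of mean egg counts to the non-cured needs changing whatever the correlation, because that group is selected after randomization.

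**What to change.** 1. **Hemoglobin and weight.** Pre-specify, as the main analysis and not as a conditional one, either ANCOVA at each visit with arm and the child's baseline value, or a linear mixed model with arm, visit, arm-by-visit and the child's baseline value. The mixed model also keeps children who miss one visit; the Withdrawal section says that such children remain in the study.
2. **Egg counts.** Compute and compare arithmetic means on all children with a stool result at the visit, with cured children counted as zero. Keep the egg reduction rate as a ratio of arithmetic means.
3. **If egg counts are modelled.** Use a count model such as negative binomial, with the baseline count as a covariate. Use log(EPG + 1) at most as a sensitivity analysis.
4. **If ANOVA is retained anywhere.** State whether it is on change scores or repeated-measures, so that it cannot be read as treating visits as independent.

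The cost is a few sentences of analysis text. The baseline and follow-up measurements are already in the visit schedule, and no procedure or sample size changes. Because the analysts are unblinded, the change should be dated and should record whether outcome data by arm had been examined.

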**Methods:**

The SCHISTOACT study is an open-label, head-to-head, five-arm, proof-of-concept, non-inferiority, individually randomized controlled trial with a follow-up of 12 weeks. A total of 540 primary school-aged children from the Mwea area, Kirinyaga County in central Kenya, diagnosed with *S. mansoni* infection (by Kato-Katz method) are randomly allocated (1:1:1:1:1) to a single dose of praziquantel plus a 3-day course of artesunate-sulfalene/pyrimethamine, or artesunate-amodiaquine, or artesunate plus mefloquine, or dihydroartemisinin-piperaquine, or praziquantel control arm. The primary endpoints are efficacy (cure rate, assessed by microscopy) and safety (adverse events) of each study arm 6 weeks after treatment. Secondary endpoints include cumulative cure rate, egg reduction rate, and re-infection 12 weeks after treatment. The non-inferiority margin is set at − 10 for the risk difference in cure rates between praziquantel and the combined treatment.

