## Methods

### Study objectives

The overall purpose of the SCHISTOACT study is to evaluate the role of combination therapy in treating schistosomiasis. The primary objective of the study is to evaluate the efficacy (assessed as cure rate by microscopy) and safety (frequency of adverse events) of a single dose of praziquantel combined with a 3-day course of artesunate plus sulfalene/pyrimethamine or artesunate plus amodiaquine or artesunate plus mefloquine or dihydroartemisinin-piperaquine compared with single-dose praziquantel in the treatment of children with confirmed *Schistosoma mansoni* infection.

Our secondary objectives are as follows:To assess the cumulative cure rate at 12 weeks after treatmentTo assess the egg reduction rate at 6 and 12 weeks after treatmentTo assess the re-infection rate at 12 weeks after treatment

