### Outcomes

The primary efficacy outcomes are as follows:Cure rate at week 6 after starting study treatments, as assessed by microscopy. The cure rate on each PZQ plus ACT arm is compared with that on the PZQ alone arm.The number of participants with drug-related adverse events in the first 24 h after study treatment.

The secondary outcomes are as follows:Cumulative cure rate at week 12 after enrollment, as assessed by microscopy. The cure rate on each PZQ plus ACT arm is compared with that on the PZQ alone arm.Egg reduction rate at weeks 6 and 12 after starting treatment, as assessed by microscopy and intensity reduction rate, comparing each PZQ plus ACT with PZQ alone arm.The prevalence of re-infection at 12 after starting treatment, as assessed as the number of children who were cured at week 6 follow-up but positive for *S. mansoni* at the week 12 follow-up, compared each PZQ plus ACT arms to the PZQ alone arm.

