## Discussion

THE SCHISTOACT is the first clinical trial to compare the efficacy and safety of praziquantel plus four artemisinin-based combinations with praziquantel alone in treating African children with intestinal schistosomiasis. The role of artemisinin-based combination therapies in schistosomiasis control cannot be deduced from the available scanty evidence. Due to the differences in the mechanism of drug action, combination therapy using praziquantel plus an ACT has the potential to support the move from morbidity to transmission control, thus accelerating the global schistosomiasis elimination agenda. If the effectiveness and safety are confirmed, combination therapy is likely to be useful for schistosomiasis control in malaria-free settings, in patients with both malaria and schistosomiasis, as chemoprophylaxis for travelers to schistosomiasis-endemic areas, and as second-line treatment in cases of praziquantel failure. The strength of this study lies in the head-to-head comparison to contribute comprehensive evidence from a single study regarding the comparative efficacy and safety of praziquantel combined with four different artemisinin-based combination therapies in the treatment of *S. mansoni*. Overall, this study will contribute much-needed evidence to inform the global policy on the role of artemisinin-based combination therapies in schistosomiasis control.

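### Safety compared with praziquantel alone is part of the primary objective, but the stated primary safety analysis is per-arm counts and percentages, with no between-arm estimate or measure of uncertainty

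*Protocol article*

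**What the plan says.** All references are to the Protocol article.

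- **Study objectives.** The primary objective includes "safety (frequency of adverse events) of a single dose of praziquantel combined with a 3-day course" of an ACT, "compared with single-dose praziquantel in the treatment of children with confirmed" *S. mansoni* infection. The comparison with praziquantel applies to efficacy and safety alike.
- **Abstract, Methods.** "The primary endpoints are efficacy (cure rate, assessed by microscopy) and safety (adverse events) of each study arm 6 weeks after treatment".
- **Outcomes.** The second primary outcome is "The number of participants with drug-related adverse events in the first" 24 h after treatment. The cure-rate, egg-reduction and re-infection outcomes are each stated as compared with the PZQ arm. The adverse-event outcome is not.
- **Data management and analysis.** For what the document itself calls the primary safety analysis, "the frequency and pattern of adverse events are computed by patient counts and percentages in each of the five treatment groups", among children who received at least one dose. For cure rate, the same section specifies absolute risk differences with 95% CIs and a margin of −10. It also sets a general rule that a two-sided p-value "less than 0.05 is considered statistically significant for all tests", but names no test for adverse events.
- **Sample size.** The calculation rests on cure rate alone.
- **Discussion.** "If the effectiveness and safety are confirmed, combination therapy is likely to be useful for schistosomiasis control in malaria-free settings".

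**The concern.** The objective asks how the adverse-event frequency on each combination compares with that on praziquantel alone. The stated analysis describes each arm on its own. It produces neither an estimate of the difference nor any statement of how large an excess the data leave open. For cure rate the plan does both.

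This goes beyond a detail left to a later analysis plan. The document names its primary safety analysis and says what it consists of, and an analysis plan that followed that text would contain no comparative safety estimate.

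At stake is how much a comparative safety conclusion can bear. The trial was sized for cure rate, so nothing in the plan tells a reader whether similar percentages in two arms are informative or merely imprecise.

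**Working it through.** **Inputs**

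- Arm size: 102 per arm, 5% loss, 108 randomized per arm, 540 in total (Sample size).
- Safety population: at least one dose received, so at most 108 per arm (Data management and analysis).
- Adverse-event rates: none in the document. A range of 5% to 50% is assumed.

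**Step 1: the plan's own figure.** 102 / 0.95 = 107.4, rounded up to 108, and 5 × 108 = 540. Both agree with the document. No power or precision is stated for safety, so there is no safety figure to reproduce. How the 102 itself was derived is a separate question on which this point does not depend.

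**Step 2: what equal percentages leave open.** If two arms of n = 108 show the same event proportion p, the estimated difference is zero and the upper 95% limit equals the half-width:

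half-width = 1.96 × √(2p(1 − p)/108)

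At p = 0.10: 1.96 × √(0.18/108) = 1.96 × 0.0408 = 0.080.

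At p = 0.30: 1.96 × √(0.42/108) = 1.96 × 0.0624 = 0.122.

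| Assumed event rate in both arms | 95% CI half-width (points) |
|---|---|
| 5% | 5.8 |
| 10% | 8.0 |
| 20% | 10.7 |
| 30% | 12.2 |
| 40% | 13.1 |
| 50% | 13.3 |

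**Step 3: events not seen at all.** For 0 events in 108 children, the upper limit of the exact two-sided 95% CI is 1 − 0.025^(1/108) = 3.36%.

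**Step 4: cure rate and adverse events side by side.**

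| | Cure rate | Adverse events |
|---|---|---|
| Part of the primary objective, against praziquantel | yes | yes |
| Primary outcome | yes | yes |
| Between-arm estimate stated | risk difference | none |
| Interval stated | 95% CI | none |
| Basis of sample size | yes | no |

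**The case against.** The strongest reply is that the document is a journal article, that adverse events are usually tabulated descriptively, and that intervals can be left to an analysis plan. The Outcomes section defines the safety outcome as a number of participants without adding a comparison, and side-by-side percentages that include the randomized praziquantel arm are a comparison of a kind. The difference and its CI can also be worked out from the counts that the plan already requires. Severity, causality and outcome of each event are recorded too, so percentages are not the only safety information.

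Much of this stands. Descriptive tables are not wrong in themselves, a formal safety margin is not obligatory, and an analysis plan that is not shown may add the comparison. What remains is that the named primary safety analysis does not estimate the contrast that the primary objective states. That the missing estimate can be computed from planned data shows the remedy is cheap; it does not show that the plan provides it.

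Three stronger readings are tempting, and the document does not support them:

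- *That a non-significant difference will be reported as safe.* No section says so. The 0.05 level is a general rule, and no adverse-event test is named.
- *That the Discussion sets a decision rule for safety.* The sentence is conditional and concerns possible later use. It is neither a criterion nor a planned conclusion.
- *That a harmful excess would usually be missed.* With a two-sided 5% chi-square test at 108 per arm, detection is 55% for 10% v 20%, 29% for 5% v 10%, 40% for 20% v 30%, 34% for 30% v 40% and 63% for 30% v 45%. In two of these five assumed scenarios the excess is detected more often than not, and the plan does not specify this test for adverse events anyway.

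**Conclusion.** The point holds as a mismatch between objective and analysis. Comparative safety is part of the primary objective, and the stated primary safety analysis contains no between-arm estimate or measure of uncertainty. On their own, the planned percentages would be weak support for a comparative safety conclusion, because an excess of the size shown in the half-width table could lie behind equal percentages.

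The sizes rest on full arms of 108, on the normal approximation for the difference, and on assumed event rates. If fewer children are dosed, the intervals widen slightly. The judgement concerns the document as shown. It does not say that the trial cannot examine safety, nor that its authors will misread the result.

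**What to change.** In the primary safety paragraph of Data management and analysis, keep the counts and percentages and add:

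- for each PZQ plus ACT arm, the risk difference against PZQ alone, with its 95% CI, in the proportion of children with the primary safety outcome as the Outcomes section defines it (drug-related events in the first 24 h);
- the same estimate for children with any adverse event, since the abstract and the analysis paragraph do not carry the drug-related and 24 h limits;
- exact 95% CIs for severe and for serious events.

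State that any safety conclusion will be worded from the upper limits of these intervals, that is, by the size of excess that the data exclude, and that absence of a significant difference will not be taken as evidence of safety. A formal safety margin is not required.

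The cost is a wording change and one added table, from data already being collected, with no extra children or visits. The downside is a more modest safety statement.
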